# Efficacy and safety of dual intravenous artesunate plus quinine compared to intravenous artesunate for cerebral malaria in a triple blinded parallel multisite randomized controlled trial in Nigerian children: DUAL PAQ TRIAL Protocol

**DOI:** 10.1186/s13063-021-05634-6

**Published:** 2021-10-20

**Keywords:** Cerebral malaria, Artesunate, Quinine, Randomized controlled trial, Blinding

## Abstract

**Background:**

Evidence exists as to the criticality of the first 24 h in the management of cerebral malaria. The morbidity and the mortality rate (35%) with the current intravenous monotherapy for the initial treatment of cerebral malaria are unacceptably high. Combination therapy and a shorter course of effective medication have been shown to improve outcomes in human participants in the treatment of other diseases. This study outlines a protocol to conduct a triple blinded parallel randomized controlled trial on cerebral malaria using dual intravenous medications compared to the current standard of monotherapy.

**Methods:**

This is a parallel multi-site randomized controlled superiority triple blinded trial consisting of intravenous artesunate plus quinine and a control arm of intravenous artesunate only. Eligible and assenting children aged 6 months to 17 years will be recruited from 4 tertiary hospitals by random selection from the list of tertiary hospitals in Nigeria. Participants will be randomized and assigned in parallel into two arms using random numbers generated from GraphPad Prism (version 9) by a clinical pharmacologist who has no link with the investigators, the patients, or the statistician. The primary measurable outcome is survival at 12, 24, and 48 h post-randomization. A composite secondary outcome consists of the number of children that regained consciousness, parasitaemia and defervescence at 12 and 24 h post-randomization and haematological and inflammatory markers at 24 and 48 h post-randomization. Adverse events both solicited and unsolicited are recorded all through the study post-randomization. The study is approved by the State Research Ethics Review Committee. Data analysis will be performed in GraphPad Prism version 9.

**Discussion:**

The outcome of this analysis will give insight into the efficacy and safety of dual intravenous antimalaria in the treatment of cerebral malaria among Nigerian children compared with the standard of care. The safety profile of this intervention will also be highlighted. This may help inform physicians on the optimal treatment for cerebral malaria to improve outcomes and reduce recrudescence and treatment failure.

**Trial registration:**

Pan Africa Clinical Trial Registry PACTR202102893629864. 23/02/2021.

**Supplementary Information:**

The online version contains supplementary material available at 10.1186/s13063-021-05634-6.

## Administrative information

Administrative details of DUAL PAQ.

## Background and rationale {6a}

Malaria remains a global health problem and a threat to human survival in over one hundred countries of the world [1–6]. It is one of the leading causes of morbidity and mortality among the under-five in sub-Saharan Africa [1]. In spite of the concerted efforts and huge resources dedicated to malaria eradication, its tales of woes remains strong and visible [1, 3, 7]. The socio-economic burden of malaria in endemic communities, especially in sub-Saharan Africa, is still colossal. It is a major source of drain to the scarce resources in low- and middle-income countries (LMIC) of the world [7].

Reports from previous studies [1, 2, 7] have shown that severe/complicated malaria carries 100% mortality if untreated. The most critical moment determining outcomes of severe malaria is the first 24 h from disease onset, often characterized by multiple organ dysfunction syndrome [1, 2]. However, current treatment regimens use monotherapy that provides an opportunity for the development of drug resistance and sub-optimal outcome [7]. Current mortality from severe malaria ranges between 22.5 and 34.7% in Africa and Asia, respectively [1, 8–10]. Although there has been some improvement in outcomes [1, 8, 11], the high morbidity and mortality in the endemic countries are still concerning.

The current treatment for uncomplicated malaria advocates artemisinin-based combination therapy. However, the question is whether the use of dual artemisinin-based intravenous antimalarials is more efficacious than the current monotherapy. Indices of comparison consist of survival, recovery of consciousness, parasite clearance, fever resolution and adverse events in cerebral malaria. We hypothesize that initiation of intravenous artesunate plus quinine within the first 24 h of cerebral malaria will be more efficacious than intravenous artesunate only [9, 10]. This protocol describes a parallel multisite randomized triple blinded controlled trial to compare intravenous artesunate plus quinine with artesunate only in Nigerian children aged 6 months to 17 years.

## Definition of terms

Cerebral malaria (WHO guidelines for malaria, 2021) is severe *Plasmodium falciparum* malaria with impaired consciousness (Glasgow Coma Scale < 11, Blantyre Coma Scale < 3) persisting for > 1 h after a seizure.

Impaired consciousness is a Glasgow Coma Score < 11 in adults or a Blantyre Coma Score < 3 in children.

## Research problem

Severe malaria with multiple organ dysfunction is a major killer of children under-five in sub-Saharan Africa [1]. The morbidity and mortality rate of 35% with the current monotherapy is unacceptably high [8]. There is a need for modification of the current treatment regimen to improve outcomes and prevent the development of resistance, recrudescence and treatment failure.

## Rationale for the study

Combination therapy and a shorter course of effective medication in the treatment of diseases have been shown to improve outcomes in human immunodeficiency virus AID (HIV-AID) infection, tuberculosis, acute pyogenic infections and epilepsy [12–15]. If the critical time for severe malaria treatment is the first 24 h of illness, aggressive therapy targeted during this time using a synergistic combination of intravenous artesunate-quinine has a potential for rapid parasite clearance and reduce morbidity and mortality. This trial is feasible because of the long-standing biosafety profiles of artesunate and quinine. We are optimistic that the results of this trial may stimulate the interest of pharmaceutical companies in the development of newer formulations of intravenous antimalarial combination therapies; this could improve the availability and administration of treatment within the first 24 h and consequently improve the health outcomes in patients diagnosed with cerebral malaria.

## Objectives {7}

### General objective

The general objective is to determine the efficacy and safety of dual intravenous artesunate plus quinine combination regimen against the monotherapy of artesunate in the treatment of cerebral malaria.

### Specific objectives

The specific objectives are to determine the following:
Survival rate from cerebral malaria on dual intravenous artesunate plus quinine compared to intravenous artesunate onlyThe parasite clearance rate measured by microscopyFever defervescence, measured by axillary temperatureTime to recovery of consciousnessTime to the conversion of dual intravenous treatment to a full dose of enteral artemisinin-based combination therapySide effect profile of interventions (treatment and control arms)Neurologic status at the fourth week

## Trial design {8}

This will be a triple blinded, parallel randomized controlled trial consisting of one treatment (experimental arm: intravenous artesunate + quinine) and one control arm (intravenous artesunate). Patient allocation will be in the ratio of 1:1. The assignment of patients into the study arms will be randomized.

## Methods: participants, interventions, and outcomes

The participants’ flow chart from invitation through enrolment, allocation, and assessment is shown in Fig. 1

**Fig. 1 Fig1:**
[figure not shown]
Participant flow chart

### Study setting {9}

This study is a multi-centre RCT involving 4 tertiary hospitals (one private and three public) located in three of the six geopolitical regions in Nigeria [16, 17]. The selected tertiary hospital includes University College Hospital, Ibadan; Bowen University Teaching Hospital, Ogbomoso; the Federal Medical Centre Katsina, Katsina State; and the University of Maiduguri Teaching Hospital, Maiduguri.

All the facilities have the human capacity to manage critically ill children. Other details are given: administrative details (the ‘Administrative information’ section) and trial site locations (Fig. 2).

**Fig. 2 Fig2:**
[figure not shown]
Trial site locations

### Eligibility criteria {10}

#### Inclusion criteria

Children between the ages of 6 months and 17 years as at the last birthday.Children with impaired consciousness (Glasgow Coma Scale < 11 for children older than 5 years or Blantyre Coma Scale < 3 children younger than 5 years) persisting for > 1 h after a seizure in the presence of demonstrable peripheral asexual *P. falciparum* parasitaemia. This is in line with the WHO guideline for malaria, 2021.

#### Exclusion criteria

Children with mixed species of *Plasmodium* infectionPrior treatment with artemisinin derivatives or quinine or other antimicrobial with antimalarial activities including other antimalaria or antibiotics within 12 h of screeningChildren with positive biochemical and/or microbiological cerebrospinal fluid analysis result consistent with a diagnosis of meningitisChildren who have intracranial infections or intracranial space-occupying lesionsChildren with previous neurological deficit either focal or globalChildren whose caregivers declined granting consent for their participation in the study

### Who will take informed consent? {26a}

Prior to recruitment, the research will be explained to the parents/caregivers by the investigators who will obtain written informed consent. Parents/caregivers will be informed of their freedom to refuse to take part in the study without any negative consequences to them or their wards in the course of the treatment.

### Additional consent provisions for collection and use of participant data and biological specimens {26b}

Additional consent will be obtained for data availability for secondary analysis and for ancillary studies on biological specimens collected for the research.

### Interventions

#### Intervention description {11a}

The experimental arm will receive a combination of intravenous quinine plus artesunate. A clinical pharmacologist (unblinded) will deliver the allocated treatment to the clinician (blinded) for administration.

This group will receive a combination of intravenous quinine plus artesunate. The quinine will be given at a loading dose of 20 mg/kg and subsequently 10 mg/kg 8 h for 72 h. However, if the patient remains unconscious, the dose will be reduced to 7.5 mg/kg 8 hourly until he/she regains consciousness. In parallel, intravenous artesunate at 3 mg/kg if weight is less than 20 kg or 2.4 mg/kg if weight is greater than 20 kg at 0, 12, and 24 h and subsequently a daily dose of 1.2 mg/kg/day until conscious.

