#### Control arm: intravenous artesunate only

This arm will receive intravenous artesunate at 3 mg/kg if weight is less than 20 kg or 2.4 mg/kg if weight is greater than 20 kg at 0, 12, and 24 h and subsequently a daily dose of 1.2 mg/kg/day until conscious. Additionally, intravenous 10% dextrose water will be given in lieu of intravenous quinine.

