#### All the groups

The two groups will receive enteral artemisinin-based combination therapy (ACT) as soon as they regain consciousness and can tolerate the full course of oral ACT in line with WHO recommendation.

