#### Secondary outcomes

Number of patients that regained full consciousness as measured by GCS/MGCS of > 11 for children > 5 years or Blantyre Coma Scale of > 3 in children < 5 years at 12 and 24 h post-randomization.Number of patients with asexual form of malaria parasite present or absent at 12 and 24 h post-randomization.Number of patients that achieved fever defervescence (attainment and sustenance of axillary temperature of < 37.5 °C) at 12 and 24 h post-randomization.Parasite density at 12 and 24 h post-randomization.Number of patients with neurologic deficits at the fourth week (day 29) post-intervention in each of the arms. Neurology deficit is defined as the presence of impaired cognitive, motor or cranial nerve palsy and or persistence of convulsions.Time to convert to a full dose of enteral artemisinin-based combination therapy.The side effect profile (adverse events and serious adverse events) of medication in each arm of study: (i) solicited side effects include hypoglycaemia, arrhythmia, thrombocytopenia, tinnitus and anaemia; (ii) unsolicited adverse events as reported by patients post-randomization; (iii) random plasma glucose will be measured 6 hourly until 48 h after parasite clearance. Hypoglycaemia will be corrected with 2-4 ml/kg of 10% D/W and maintenance with glucose infusion at 6–8 mg/kg/min until euglycaemic; (iv) electrocardiography will be recorded before the administration of anti-malaria and 4 h after an intervention. The QT and RR will be measured by software and checked manually. Bazett’s formula will be used to correct the QT interval (QTc = QT/RR**0.5). Prolonged QT interval managed as per hospital protocol; (v) haematocrit, serum ferritin, platelet count and erythrocyte sedimentation rate will be monitored at baseline and 24 h and 48 h post-randomization.Plasma levels of inflammatory markers including C reactive protein, procalcitonin, lactate dehydrogenase and interleukin 6 at baseline, 24 h, and 48 h. Inflammatory markers and cytokine are included to assess a possible ‘cytokine storm’ in the course of parasite clearance.

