**Interventions**							
*Artesunate + quinine—8 hourly*	x	x	x	x	x	…	
*Artesunate—12 hourly*	x	x	x	x	x	…	

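### The treatment sections give incompatible rules for when intravenous quinine ends relative to oral ACT, so quinine exposure, per-protocol adherence and time to ACT are not uniquely defined

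*Protocol article*

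**What the plan says.** All references are to the protocol article.

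- **Quinine course.** Intervention description {11a}: "The quinine will be given at a loading dose of 20 mg/kg and subsequently 10 mg/kg 8 h for 72 h". The next sentence adds a reduction: "if the patient remains unconscious, the dose will be reduced to 7.5 mg/kg 8 hourly until he/she regains consciousness". No time is given at which a child counts as still unconscious.
- **Switch to oral treatment.** All the groups: "The two groups will receive enteral artemisinin-based combination therapy (ACT) as soon as they regain consciousness", subject to tolerating the oral course. The rule covers both arms and does not mention quinine or the sham.
- **Conversion as an objective and outcome.** Specific objectives describes the time until the dual intravenous treatment is converted to ACT. Secondary outcomes lists "Time to convert to a full dose of enteral artemisinin-based combination therapy".
- **Discontinuation.** The criteria in {11b} include full recovery after initial treatment, without saying which drugs stop.
- **Sham.** The control arm receives 10% dextrose in place of quinine, and the comparator section says that this is to keep administration similar. Neither section gives its duration.
- **Artesunate.** The text for both arms gives it "at 0, 12, and 24 h and subsequently a daily dose of 1.2 mg/kg/day until conscious". The rows of the Participant timeline are labelled "Artesunate—12 hourly" and "Artesunate + quinine—8 hourly".
- **Analysis.** The section on protocol non-adherence and missing data says that the results will be analysed per protocol.

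**The concern.** A fixed 72 h quinine course and a switch to oral ACT on waking are two different rules for ending intravenous treatment. For a child who wakes and tolerates oral treatment before 72 h, the article does not say which rule governs. This is a conflict between stated rules, not a detail that a condensed article leaves to the full protocol.

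Three things depend on the answer:

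1. **Exposure to the experimental drug.** Quinine is the only active difference between the arms. The solicited events include hypoglycaemia, arrhythmia and tinnitus, and signs of quinine toxicity trigger unblinding. If four hospitals follow different sections, they test different regimens under one label.
2. **Who counts as adherent.** With a per-protocol analysis, a child whose quinine stopped at 24 h is adherent under one section and a deviation under another. Membership of the analysis set is then open to interpretation.
3. **Time to ACT.** This secondary outcome cannot be interpreted until it is settled whether ACT may start while intravenous drug or sham is still running.

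The missing sham duration belongs to the same problem, because the sham stands in for quinine and takes on whatever ambiguity quinine has. The article also uses 10% dextrose to correct hypoglycaemia, so how long the sham runs could bear on a solicited safety outcome.

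**Working it through.** The article gives no total-exposure figure to reproduce, and the sample size of 470 is not touched by this point. The check lays the readings side by side and counts doses under each.

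**Inputs** (Intervention description {11a}): loading dose 20 mg/kg at 0 h; maintenance 10 mg/kg every 8 h; course length 72 h; reduced dose 7.5 mg/kg every 8 h. Assumed for illustration: a child who is conscious and tolerates oral treatment at 24 h.

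**Formula.** Total quinine = 20 + 10 × (number of maintenance doses).

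| Count | Quinine stops at the 24 h switch | Quinine runs to 72 h | Ratio |
|---|---|---|---|
| Doses before the stop time | 8, 16 h: 20 + 2×10 = 40 mg/kg | 8 to 64 h: 20 + 8×10 = 100 mg/kg | 100/40 = 2.5 |
| Including the dose at the stop time | 8, 16, 24 h: 20 + 3×10 = 50 mg/kg | 8 to 72 h: 20 + 9×10 = 110 mg/kg | 110/50 = 2.2 |

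The same counting convention must be used for both stop times, so the like-for-like range is 2.2 to 2.5.

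**By 48 h**, when the primary outcome is measured, on the first count: 40 mg/kg if stopped at 24 h, against 20 + 5×10 = 70 mg/kg if continued (doses at 8, 16, 24, 32 and 40 h).

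**Dose reduction.** Take a child unconscious throughout the 72 h, on the first count. If the reduction applies only after 72 h, the total is 20 + 8×10 = 100 mg/kg. If it applied from the first maintenance dose (an assumption, taken as the lower bound), it is 20 + 8×7.5 = 80 mg/kg. The text does not place the change within this range.

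**Time to ACT under each reading:**

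- Quinine stops at the switch: no minimum time in either arm.
- Quinine overlaps with ACT: no minimum time in either arm.
- ACT waits for quinine, and the sham runs as long as quinine and also delays ACT: a 72 h minimum in both arms.
- ACT waits for quinine but not for the sham: a 72 h minimum in the dual arm only.

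Only the last reading separates the arms by construction. The article neither states nor excludes it.

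**Artesunate** for a child unconscious through 72 h. The text gives doses at 0, 12, 24, 48 and 72 h, five in all: 3×3 + 2×1.2 = 11.4 mg/kg below 20 kg, or 3×2.4 + 2×1.2 = 9.6 mg/kg above. A literal 12-hourly reading gives seven doses: 13.8 or 12.0 mg/kg if each later dose is 1.2 mg/kg (assumption), and 21.0 or 16.8 mg/kg if the initial dose is repeated (assumption). The timeline marks fall at 0, 12, 24, 48 and 72 h, which fits the text, and there is no 36 or 60 h column. The conflict therefore lies in the row labels alone, and dosing up to 24 h agrees between the text and the 12-hourly label.

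**The case against.** **The documents lean towards one reading.** The objective speaks of converting the dual intravenous treatment, and full recovery is listed under discontinuation. Both suggest that intravenous drug ends at the switch. This narrows the ambiguity, but it does not cancel the explicit 72 h, and neither section names quinine. Likewise, the reduction sentence directly follows the 72 h course and can be read as applying after it, but no time is written.

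**The primary comparison is little exposed.** Survival is measured at 48 h, and the conflict over the switch arises only in children already awake. Consciousness, parasitaemia and fever are assessed at 12 and 24 h. This largely stands: no effect on the survival comparison or on the sample size is shown. Two routes stay open: the per-protocol set, and the undated dose reduction, which concerns children still unconscious.

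**Sites need not diverge.** Treatment is boxed and supplied by a central pharmacologist, a 20-patient pilot is followed by step-down training, and sites are monitored weekly. So divergence is possible, not certain. These measures can only enforce a rule that has been written.

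**A stronger inference to avoid.** A reader might conclude that the dual arm cannot convert before 72 h while control converts on waking, so that time to ACT is partly fixed by arm, with a delay of up to 72 − 24 = 48 h for a child awake at 24 h. The documents do not support this. The quinine sentence does not mention ACT, the switch rule covers both groups, clinicians are blinded, and control receives a sham. A clinician who cannot tell the arms apart cannot hold back ACT in only one of them, unless the sham's duration gives the arm away.

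**Conclusion.** The point holds as a contradiction over when intravenous treatment ends. The fixed quinine course, the switch rule, the conversion objective and the discontinuation criterion are not reconciled, the dose reduction has no time point, and the sham has no duration.

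For a child ready for ACT at 24 h, the readings differ 2.2- to 2.5-fold in total quinine, and 40 against 70 mg/kg by 48 h. These figures describe one illustrative child. The article does not say how many children wake before 72 h, so the effect on average exposure cannot be sized. Adherence for the per-protocol analysis and the time-to-ACT outcome both depend on the unsettled rule. Bias between arms in time to ACT is conditional on how the sham is handled and is not established.

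The artesunate discrepancy is minor: two row labels disagree with consistent text and consistent table marks. The main conflict should be settled before recruitment, because it concerns the experimental drug itself.

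**What to change.** Reconcile Specific objectives, Intervention description {11a}, the control-arm section, All the groups, the discontinuation criteria {11b} and the Participant timeline, so that they give one schedule per arm. That schedule should state:

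- one rule, identical and blinded in both arms, for when intravenous drug and sham stop relative to the start of ACT;
- the duration of the sham;
- the time point at which the quinine reduction applies;
- timeline row labels that match the text.

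Then define time to ACT and per-protocol adherence from that rule. The clinical team decides the content, and no schedule is endorsed here.

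The cost is amendment wording and matching changes to site training material. The article lists the trial as active but not recruiting. The sample size does not change.

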#### Explanation for the choice of comparators {6b}

Intravenous artesunate alone will be used as a comparator in this study. The choice of the two antimalaria is based on the difference in pharmacodynamics and varying mechanism of actions of the artemisinin derivatives compared with quinine. It is assumed that a synergistic action of the combined drugs against the erythrocytic and gametophyte stages of malaria parasite may enhance clearance. In addition, quinine is the only licenced alternative intravenous antimalaria by the WHO besides the artemisinin derivatives. These are the current standard treatments for cerebral malaria by the World Health Organization. In order to facilitate blinding, the monotherapy group (control) will also receive intravenous dextrose water or water for injection to maintain the similarity of treatment administration with the dual-therapy group (the treatment arm).

